### **IMP reporting pathway - SUSAR Reporting**

The CRO, on behalf of the sponsor, will inform the MHRA and the REC of SUSARs within the required expedited reporting timescales (15 days for all SUSARs, unless resulting in death or is life threatening in which case 7 days, with a final report within a further 8 days (total 15)). The sponsor will also inform all Investigators concerned of relevant information about SUSARs that could adversely affect the safety of participants.

### **Device reporting pathways**

All SAEs and DDs (meeting criteria below) will be reported to the MHRA devices sector, by the CRO, using the MEDDEV SAE reporting form (MEDDEV 2.7/3). Timelines outlined below;

| Term                        | Reporter     | Reported to | Reporting Timeline from awareness of the event                                                                                                                                                                                                                        |
|-----------------------------|--------------|-------------|-----------------------------------------------------------------------------------------------------------------------------------------------------------------------------------------------------------------------------------------------------------------------|
| Device Deficiency (DD)      | Investigator | Sponsor/CRO | Immediately/within 24 hrs of becoming aware of event.                                                                                                                                                                                                                 |
|                             | Sponsor/CRO  | MHRA        | Immediately but no later than 2 calendar days if the event may have led to an SAE if; 
 
• suitable action had not taken
 
• intervention had not been made
 
• if circumstances had been less fortunate
 
 |
| Serious Adverse Event (SAE) | Investigator | Sponsor/CRO | Immediately/within 24 hrs of becoming aware of event.                                                                                                                                                                                                                 |
|                             | Sponsor/CRO  | MHRA        | Immediately but not later than 2 calendar days of sponsor becoming aware of event if event indicates an imminent risk of death,                                                                                                                                       |

|                                                             |              |             |                                                                                                                                                                                                                                                                    |
|-------------------------------------------------------------|--------------|-------------|--------------------------------------------------------------------------------------------------------------------------------------------------------------------------------------------------------------------------------------------------------------------|
|                                                             |              |             | 
serious injury, or serious illness and that requires prompt remedial action for other patients, users or persons, or a new finding to it.
 
For all other events
Immediately but not later than 7 calendar days of sponsor becoming aware of event
 |
| Serious Adverse Event (USADE)                               | Investigator | Sponsor/CRO | Immediately/within 24 hrs of becoming aware of event.                                                                                                                                                                                                              |
|                                                             | Sponsor/CRO  | REC         | Within 15 calendar days of becoming aware of the event                                                                                                                                                                                                             |
| New findings/updates in relation to already reported events | Sponsor/CRO  | MHRA        | Immediately but not later than 7 calendar days of sponsor becoming aware of event                                                                                                                                                                                  |

[figure not shown]

## 9.4 Responsibilities

### Principal Investigator (PI):

Checking for and assessing AEs when participants are admitted to hospital or return for follow-up.

1. Using medical judgement in assigning severity, seriousness, causality and expectedness as per approved IB for the trial.
2. Ensuring that all SAEs are recorded and reported to the sponsor within 24 hours of becoming aware of the event and provide further follow-up information as soon as available.
3. Ensuring that SAEs are chased with Sponsor if a record of receipt is not received within 2 working days of initial reporting.
4. Ensuring that AEs are recorded and reported to the sponsor in line with the requirements of the protocol.

### Chief Investigator (CI) / delegate or independent clinical reviewer:

1. Clinical oversight of the safety of patients participating in the trial, including an ongoing review of the risk / benefit.
2. Using medical judgement in reviewing all SAEs (seriousness, causality and expectedness in line with approved IB.
3. Immediate review of all SUSARs/USADEs.
4. Review of specific SAEs /SARs/SADEs in accordance with the trial risk assessment and protocol as detailed in the Trial Monitoring Plan.
5. Assigning Medical Dictionary for Regulatory Activities (MedDRA) or Body System coding to all SAEs.
6. Preparing the clinical sections and final sign off of the Development Safety Update Report (DSUR).
7. Reviewing the quarterly safety reports to the device sector

### Sponsor:

1. Central data collection and verification of all safety events according to the trial protocol onto a database – oversight, delegated to CRO
2. Reporting safety information to the CI, delegate or independent clinical reviewer for the ongoing assessment of the risk / benefit according to the Trial Monitoring Plan.
3. Reporting safety information to the independent oversight committees identified for the trial according to the Trial Monitoring Plan.
4. Expedited reporting of SUSARs/USADEs to the Competent Authority (MHRA in UK) and REC within required timelines – oversight, delegated to CRO
5. Notifying Investigators of SUSARs/USADEs that occur within the trial oversight, delegated to CRO.
6. Checking for (annually) and notifying PIs of updates to the Reference Safety Information for the trial.

Preparing standard tables and other relevant information for the DSUR in collaboration with the CI and ensuring timely submission to the MHRA and REC CRO

The appointed CRO will be responsible for project management of the trial (on behalf of the Sponsor). The CRO will be responsible for review of study documents to be submitted for ethics/regulatory approvals, tracking the progress of the study and timelines, SAE tracking and management, safety reporting to device sector, expedited safety reporting (SUSARs/USADEs), site initiation visit and site activation, study monitoring.

#### Trial Steering Committee (TSC):

In accordance with the Trial Terms of Reference for the TSC, periodically reviewing safety data and liaising with the DSMB regarding safety issues.

#### Data & Safety Monitoring Board (DSMB):

In accordance with the Trial Terms of Reference for the DSMB, periodically reviewing overall safety data to determine patterns and trends of events, or to identify safety issues, which would not be apparent on an individual case basis. The DSMB will be responsible for authorising dose escalation.

### **9.5 Notification of deaths**

All deaths will be reported to the sponsor irrespective of whether the death is related to disease progression, the IMP, or an unrelated event. All deaths occurring during the study will be reported to the Sponsor by the investigator by emailing [[contact]](mailto:[contact]). The CRO will be copied in the correspondence. For all deaths, available autopsy reports and relevant medical reports will be made available for reporting to the relevant authorities.

### **9.6 Pregnancy reporting**

Pregnancy reporting will not be required for this study. Pregnancy is an exclusion criterion and will be confirmed at screening. As patients are hospitalised it is not expected that they will become pregnant during their participation in the treatment phase of this study.

### **9.7 Overdose**

The definition of an overdose for this study is administration of one or more additional vials in relation to the dosing schedule displayed in section 8.6.

All reports of overdose with and without an adverse event must be reported by the investigator within 24 hours to the Sponsor ([[contact]](mailto:[contact])). The CRO will be copied in the correspondence. If an SAE is associated with the overdose it will be fully described in the SAE report form by the investigator or delegate. An overdose will be recorded as a protocol deviation and recorded on the protocol deviation log.

### **9.8 Reporting urgent safety measures**

If any urgent safety measures are taken the CI/Sponsor shall immediately and in any event no later than 3 days from the date the measures are taken, give written notice to the MHRA and the relevant REC of the measures taken and the circumstances giving rise to those measures.

### **9.9 The type and duration of the follow-up of participants after adverse reactions.**

Patient's that experience an adverse reaction as a result of trial treatment will be followed up until day 28 or discharge from hospital. If additional follow up is required for safety reasons the investigator will discuss this with the participant and make appropriate arrangements. Adverse events will be recorded and reported for the duration of the patient's participation in the study. Any SUSAR will need to be

reported to the Sponsor irrespective of how long after IMP administration the reaction has occurred until resolved.

### 9.10 Development safety update reports

A Development Safety Update Report (DSUR) will be submitted by the Sponsor to the competent authority and ethics committee on the anniversary of the first approval date from the regulatory authority for the IMP.

## 10 STATISTICS AND DATA ANALYSIS

### Feasibility

The adherence to per-protocol administration of Alveofact® will be summarized overall, and by dosing regimen:

- Screening, enrolment and consenting of patients
- Number and proportion of participants with initial dose successfully administered according to protocol
- Number and proportion of participants with collection of relevant intermediate physiological outcomes and safety outcomes
- Number and proportion of participants with administration of subsequent doses according to protocol criteria
- Number and proportion of participants with collection of efficacy outcome data
- Number and proportion of participants who completed the study per protocol

### Safety

The incidence and 95% Confidence Intervals of SAEs, and Grade 3 or 4 AEs will be summarized by randomization group over the first 24 hours, and throughout the study. The number and percentage of participants with AEs will be summarized by Medical Dictionary for Regulatory Activities (MedDRA) system organ class (SOC) and preferred term (PT). Additional summaries will present the number and percentage of participants with adverse events by intensity and by relationship to surfactant treatment. Summary statistics will be generated for raw laboratory safety tests, as well as for any changes from baseline, as deemed clinically appropriate.

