#### 4 TRIAL DESIGN

This study is an exploratory, dose-escalating pilot trial to test the feasibility, safety and preliminary efficacy of aerosolized lung delivery of surfactant, a medicine with a known safety profile, to improve the oxygenation and pulmonary compliance of adult patients diagnosed with moderate to severe COVID-19 associated lung injury with increasing oxygenation requirements.

The timing of escalating dosing and assessment of clinical response is based on the rapid oxygenation response of infants with surfactant deficiency ([Collaborative European Multicenter Study Group 1988](#)) and the clinical response described in adults after endobronchial administration of surfactant in ARDS ([Walmrath 2002](#)). Nevertheless, it is acknowledged that the optimal dose required for surfactant replacement therapy in adults and the rate of clinical response in patients with COVID-19 are unknown. Therefore, we propose a dose-escalating, adaptive trial design in which the feasibility of administration of aerosolized surfactant and the clinical response in mechanically ventilated COVID-19 patients are assessed. The dosing regimen may be adjusted based on accumulating data and may depend on the dose required to achieve a clinical response and the speed with which that response is seen.

Patients will enter the study and will be randomised to 3:2 for the treatment and control arms where they will receive three doses of Alveofact® via nebulizer or the control arm where treatment will follow standard of care.

Patients in the treatment arm will be assigned into cohorts sequentially as follows:

- **COHORT 1:** 3 patients will receive 10 vials (1080 mg) each of Alveofact® at dosing times of 0 hours, 8 hours and 24 hours. 2 controls.

- **COHORT 2:** 3 patients will receive 10 vials (1080 mg) of Alveofact® at dosing times of 0 hours and 8 hours, and 30 vials (3240 mg) of Alveofact® at a dosing time of 24 hours. 2 controls
- **COHORT 3:** 3 patients will receive 10 vials (1080 mg) of Alveofact® at a dosing time of 0 hours, and 30 vials (3240 mg) of Alveofact® at dosing times of 8 hours and 24 hours. 2 controls
- **COHORT 4:** 3 patients will receive 30 (3240 mg) vials each of Alveofact® at dosing times of 0 hours, 8 hours and 24 hours. 2 controls

Control arm:

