### 7.3 The randomisation scheme

Patients will be randomised to 3:2 for the treatment and control arms using ALEA Randomisation. ALEA Randomisation is an internet-based service provided by FormsVision BV that supports online patient registration and randomisation and is fully integrated with ALEA eCRF. ALEA Randomisation has been built as a series of components, in order to support interoperability and customised extensions. The components make use of a common standard representation of data and metadata: The Operational Data Model of CDISC. Within ALEA Randomisation, the components share a database for storing and retrieving information about the trial, and a separate database for storing and retrieving patient data. ALEA Randomisation supports the following methods of randomisation for healthcare trials. It supports trials with any number of treatment groups, and randomisation ratios other than 1:1. In this study we will be using the block randomisation schema.

The following series of numbers will comprise the subject identifier:

- Three alpha characters – site code – UHS and UCH
- 2-digit subject number (e.g. 03)

Will be allocated by the site, reflecting the order of consent to the study within the site. For example, the third subject who signed an informed consent form at study UHS will be identified as Subject UHS-03.

The enrolment number will be added to the consent form at the site.

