## 8.7 Dosage modifications

In an event when the administration of 30 vials is not practical, doses may drop to 20 or 10 vials, depending on feasibility. In the event clear efficacy is observed in cohort 1, doses may drop below 10 vials or dosing times may be reduced.

Progression and dosing modifications of subsequent cohorts will be decided by teleconference of the trial steering committee. Any safety concerns would be referred to the independent DSMB on completion of dosing of each cohort of 3 patients + 24 hours to enable collection of physiological outcomes.

The DSMB will actively monitor emerging safety and efficacy data to make recommendations about early study closure or the initiation of a larger randomised controlled clinical trial.

The dose administered cannot be modified due to patient / personal legal representative request.

Given the severity of the illness in ventilated Covid-19 patients, safety data will be interpreted with caution and will not be formally compared between active intervention and control groups.

- Dosing will be stopped in individual patients upon persistent deterioration of oxygenation during or after surfactant administration
- Study stopping rules for futility or efficacy are provided in the statistical analysis section.
- The protocol team will review emerging AE/SAE/SADEs data daily. If 3 or more patients develop the same SAE after administration of study drug, the study will be paused pending review by the DSMB. The study may also pause at the discretion of the Principal Investigator if there are a significant number of unexpected AEs/SAEs/SADEs and referred to the DSMB for review.
- The DSMB will formally review the safety data after every three subjects and is available for ad hoc reviews for other safety concerns as noted above.

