### Efficacy

The goal of this study is to assess the preliminary efficacy and safety of surfactant administration, identify an efficacy signal quickly (if present) to consider initiation of a larger randomised controlled clinical trial, and assess the potential impact of total dose on preliminary efficacy.

The change in PaO2/FiO2 ratio relative to baseline at 24 hours after the last dose of surfactant and the change in Ventilation Index relative to baseline at 24 hours after the last dose of surfactant will be analysed separately. For each endpoint, a test for a total dose-response effect using a model-based multiple contrast test (Bretz et al, 2005) will be performed. Candidate dose-response models will include linear and Emax. The change in PaO2/FiO2 and change in Ventilation Index may be transformed for analysis (e.g., log transformed) to better satisfy normality assumptions of model residuals. The primary analysis will be done on patients with observed data at 24 hours ("completers"), though sensitivity analyses will also be performed if data are missing at 24 hours in an informative manner (e.g., due to death) where a non-parametric approach can accommodate missing data by assigning the worst rank.

The table below shows the power to show a significant dose response under varying assumed true dose response curves when using 12 matched controls.

| CV                                      | Relative change from baseline, on average |                           |                           |                           |                           | Power to show dose response |
|-----------------------------------------|-------------------------------------------|---------------------------|---------------------------|---------------------------|---------------------------|-----------------------------|
|                                         | Control                                   | Cohort 1 (30 total vials) | Cohort 2 (50 total vials) | Cohort 3 (70 total vials) | Cohort 4 (90 total vials) |                             |
| 20%                                     | 0%                                        | 0%                        | 0%                        | 0%                        | 0%                        | 0.05                        |

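### Section 10 tabulates SAEs and Grade 3/4 AEs by randomised arm, pooling planned totals of 30 to 90 vials, while feasibility and efficacy are broken down by dose

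*Protocol*

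**What the plan says.** Safety is the key secondary endpoint (section 3.3.2). For its main summary, section 10 (Safety) states: "The incidence and 95% Confidence Intervals of SAEs, and Grade 3 or 4 AEs will be summarized by randomization group". This is done over the first 24 hours and over the whole study. The remaining safety tables are by MedDRA class and term, the "number and percentage of participants with adverse events by intensity and by relationship to surfactant treatment", and laboratory values. None of them names dose or cohort.

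What is randomised is the arm. Section 4: "Patients will enter the study and will be randomised to 3:2 for the treatment and control arms". Section 7.3 says the same: "Patients will be randomised to 3:2 for the treatment and control arms using ALEA Randomisation". Dose is not randomised: "Patients in the treatment arm will be assigned into cohorts sequentially as follows". Each cohort has 3 treated patients and 2 controls, giving 12 and 8 in all.

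The other two parts of section 10 do use dose. Feasibility: "The adherence to per-protocol administration of Alveofact® will be summarized overall, and by dosing regimen". Efficacy is tested for a total-dose response, and the power table labels its columns by planned total, starting with "Cohort 1 (30 total vials" and ending at 90.

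**The concern.** A dose-escalation trial is expected to show how harm relates to dose. As worded, the final analysis reports efficacy by dose and safety by arm. Section 10 (Efficacy) says that significant dose-response fits can be used to estimate doses and help plan later studies. A reader of the final report would then have a dose curve for benefit and a single averaged figure for harm. Harm concentrated at the higher planned doses would be diluted in that figure, and its relation to dose could not be recovered from the table.

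**Working it through.** **Inputs.** Vials per dose come from the table in section 8.7 (Dosage schedules), with 108 mg per vial. Group sizes come from section 4. The protocol gives no expected SAE or Grade 3/4 rates.

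**1. Planned dose range, reproducing the power table's column labels.**

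| Cohort | 0 h + 8 h + 24 h | Total vials | n treated |
|---|---|---|---|
| 1 | 10 + 10 + 10 | 30 | 3 |
| 2 | 10 + 10 + 30 | 50 | 3 |
| 3 | 10 + 30 + 30 | 70 | 3 |
| 4 | 30 + 30 + 30 | 90 | 3 |

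The totals agree with the protocol. The ratio is 90/30 = 3.0, or 3,240 mg to 9,720 mg.

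The first-24-hours summary has the same spread. The doses at 0 and 8 hours total 20, 20, 40 and 60 vials in cohorts 1 to 4, again threefold. The 24-hour dose, the only one that separates cohort 2 from cohort 1, falls at or after the end of that window.

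**2. Dilution, with no rates assumed.** If all treated cohorts share a background risk and cohort k has excess e_k, then

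pooled excess = Σ(n_k × e_k) / 12.

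- Excess e in cohort 4 only: 3e/12 = 0.25e.
- Equal excess e in cohorts 3 and 4: 6e/12 = 0.50e.

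**3. The same with assumed rates.** Pooled risk for a cohort 4 excess = (9 × p0 + 3 × p1)/12.

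| Assumed background p0 | Assumed cohort 4 risk p1 | Pooled risk | True excess | Excess shown |
|---|---|---|---|---|
| 10% | 80% | 27.5% | 70 points | 17.5 points |
| 20% | 80% | 35% | 60 points | 15 points |
| 50% | 80% | 57.5% | 30 points | 7.5 points |

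**4. What the table would print.** Exact (Clopper-Pearson) limits are the 2.5% quantile of Beta(x, n−x+1) and the 97.5% quantile of Beta(x+1, n−x). Suppose events occur in 3/3 of cohort 4, 0/9 of the other treated patients and, for illustration, 2/8 controls.

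- By arm: treated 3/12 = 25% (5.5% to 57.2%); control 2/8 = 25% (3.2% to 65.1%). The rows show the same proportion.
- By cohort: 0/3, 0/3, 0/3, 3/3. The pattern is visible.

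**5. Precision of cohort rows.** 0/3 gives 0% to 70.8%; 1/3 gives 0.8% to 90.6%; 3/3 gives 29.2% to 100%. These rows can describe but cannot support inference.

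**The case against.** A reader might infer that the trial never looks at toxicity by dose, or that a higher dose could go forward with its harm unseen. The documents do not support that. Section 4 has outcomes and adverse events reviewed after each cohort, before the next dose decision. Section 8.7 (Dosage modifications) has the DSMB review safety after every three subjects and pauses the study if three or more patients develop the same SAE. These reviews see the data cohort by cohort. They govern conduct, however, and do not set what the final analysis reports.

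Nor does section 10 say that safety is summarised only by arm. It names one stratifier and excludes no others. Section 11.2 refers to a statistical analysis plan, which is not at hand and could add cohort tables. The table in section 8.7 (Dosage schedules) also heads the four dose regimens as groups. What remains is that the protocol itself fixes a stratifier, and its literal meaning is the arm because cohorts are not randomised. If the four regimens were meant, the wording still needs correcting.

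It is also tempting to express the loss as the power of a pooled test against a dose trend. Section 8.7 (Dosage modifications) rules out a formal safety comparison between arms, so no planned test loses power. Any such figures would rest on assumed event rates.

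Finally, the relationship table names surfactant but not the device. This is not a substantial gap: ADEs and SADEs are endpoints in section 3.3.2 and are device-related by the definitions in section 9.1.

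**Conclusion.** The point holds as a gap in the final safety reporting. Section 10 fixes a by-arm summary that pools a threefold planned dose range, while feasibility and efficacy are shown by dose. An excess confined to cohort 4 would appear at 25% of its size, and an equal excess in cohorts 3 and 4 at 50%. Those two factors assume three patients per cohort, the planned schedule and a common background risk; they need no event rate. The percentage-point figures do rest on assumed rates. The in-trial reviews limit the consequence to what the final report can show, and the small cohorts limit the gain to description. It is worth correcting because safety is the key secondary endpoint of an escalation trial and the change is nearly free.

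**What to change.** Amend section 10 (Safety) so that SAEs, Grade 3/4 AEs, ADEs and SADEs are presented by assigned dose cohort beside the controls, in addition to the by-arm summary, and label the cohort rows descriptive.

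Define assigned cohort as the regimen actually planned for that cohort after any steering committee change. Section 4 allows doses to be maintained or reduced between cohorts, and section 8.7 adds: "In an event when the administration of 30 vials is not practical, doses may drop to 20 or 10 vials, depending on feasibility".

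Show vials actually received in a patient listing only, and do not use them as a trend variable. Under section 8.7, further doses depend on the absence of attributable Grade 3 or 4 events, and dosing stops on persistent deterioration of oxygenation. Vials received is therefore partly a consequence of toxicity: a cohort 4 patient stopped after the first dose has received 30 vials, the same as a cohort 1 patient who completes.

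The cost is a short wording change and a few tables from data already collected. The downside is the very wide intervals, so the text should warn against reading differences between cohorts as established.

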## 8.7 Dosage schedules

Sequential vials of 108 mg Alveofact® in 2.2 mL buffer will be administered by nebulizer at 5-minute intervals with observation of vital signs, changes in oxygen saturation, FiO2 and Mean Airway Pressure. After each administration, 2 drops of normal saline will be nebulized, and the next vial administered. After administration of the first dose, dosing of Alveofact® will pause and vital signs and ventilation parameters will be assessed over the next 8 hours. If no grade 3 or grade 4 adverse events attributable to surfactant administration occur, another dose of Alveofact® will be administered and vital signs and ventilation parameters will be assessed over the next 16 hours. Again, if no grade 3 or grade 4 adverse events attributable to surfactant administration occur; a final dose of Alveofact® will be administered.

The dosing schedule for each group is displayed in the table below.

| Group | 0 Hours           | 8 Hours           | 24 Hours          |
|-------|-------------------|-------------------|-------------------|
| 1     | 10 x 108 mg vials | 10 x 108 mg vials | 10 x 108 mg vials |
| 2     | 10 x 108 mg vials | 10 x 108 mg vials | 30 x 108 mg vials |
| 3     | 10 x 108 mg vials | 30 x 108 mg vials | 30 x 108 mg vials |
| 4     | 30 x 108 mg vials | 30 x 108 mg vials | 30 x 108 mg vials |

If a dose time point is missed it should be administered as soon as it is possible. The investigator or delegate will assess the clinical stability of the patient prior to administering the dose or following a time point being missed or treatment being suspended.

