## 9.2 Operational definitions for (S)AEs/(S)ADEs

AEs, SAEs, SUSARs, ADEs, SADEs and USADEs will be recorded and reported according to applicable trial regulations.

All adverse events that occur between informed consent and until 28 days post cessation of trial treatment must be recorded in the subject notes and in the trial CRFs.

Pre-existing conditions (as recorded at screening visit) do not qualify as adverse events unless, in the opinion of the treating clinician, have worsened since baseline.

The following pre-specified respiratory deteriorations or adverse events occurring during nebulisation and occurring within 48 hours will be recorded:

1. Increase in oxygen or ventilator requirements [increase in  $FiO_2 \geq 0.2$  or more and or increase in PEEP of  $\geq 5$  or more to maintain the targeted oxygen saturation
2. Sustained deterioration in pulmonary ventilation variables  $>10\%$  (increase in peak or mean airway pressures, decrease in tidal volume)
3. Any episodes of new cardiac arrhythmia
4. Sustained reduction in mean arterial blood pressure (MAP) of  $>10\%$  or an increase in the vasopressor dose of Norepinephrine (0.1 mcg/kg/min), Epinephrine (0.1 mcg/kg/min) or the use of additional use of other inotropes (dopamine/dobutamine/milrinone) or vasopressors (vasopressin, terlipressin, phenylephrine)
5. Sustained increase in heart rate  $>20\%$
6. New bronchospasm requiring treatment

Other respiratory deteriorations: Incidence of pneumothorax (evidence on imaging), pulmonary haemorrhage (clinical), acute lobar collapse (evidence on imaging).

All SAEs and Device Deficiencies (as per definitions) must be recorded and reported to the Sponsor ([[contact]](mailto:[contact])) and CRO ([[contact]](mailto:[contact])) immediately/within 24hrs of the site becoming aware of the event.

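### The only early-window summary of SAEs and Grade 3/4 AEs stops at 24 hours, when the third surfactant dose is due, so it leaves out acute events from that dose

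*Protocol*

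**What the plan says.** Protocol Section 10 (Safety) sets two time windows: the incidence of SAEs and of Grade 3 or 4 AEs, with 95% confidence intervals, "will be summarized by randomization group over the first 24 hours, and throughout the study". It does not say when the 24 hours start and names no other early window. The same paragraph adds AE summaries by MedDRA term, intensity and relationship to surfactant, with no time limit.

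Section 4 places the doses. In cohort 1, for example, "3 patients will receive 10 vials (1080 mg) each of Alveofact® at dosing times of 0 hours, 8 hours and 24 hours". Cohorts 2 to 4 use the same three times with more vials. Section 8.7 (Dosage schedules) confirms the spacing: eight hours after the first dose, "another dose of Alveofact® will be administered and vital signs and ventilation parameters will be assessed over the next 16 hours", and the final dose follows.

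Other early horizons in the protocol run later. In Section 9.2, pre-specified respiratory deteriorations or "adverse events occurring during nebulisation and occurring within 48 hours will be recorded". Section 8.7 (Dosage modifications) times referral of safety concerns to the DSMB at completion of a cohort's dosing plus 24 hours. The co-primary endpoints in Section 3.3.1 are read at 48 hours.

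**The concern.** An early window in a trial of a nebulised product should show what happens during and shortly after dosing, before the background of critical illness swamps it. Section 2.1.2 lists hypoventilation and hypoxaemia, pneumothorax linked to compliance changes, and airway irritation as risks of a combination product with no earlier clinical experience. Safety is the key secondary objective. Section 8.7 says that safety data will not be formally compared between arms, so the descriptive tables carry the interpretation.

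As worded, the early table covers two of the three doses. A reader who takes it as the acute safety profile of the regimen would be looking at part of the regimen. Acute events after the third dose would be counted only alongside 28 days of events in ventilated COVID-19 patients, or through the relationship-to-treatment summary, which depends on the investigator's causality judgement.

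**Working it through.** **Inputs.** Vials per dose at 0, 8 and 24 hours and three treated patients per cohort (Section 4 and the table in Section 8.7); 2.2 mL per vial (Section 8.7); delivery rate of at most 0.3 mL/min (Product Characteristics, AeroFact-COVID Device).

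**Step 1: reproduce the plan's totals.** Summing the three doses gives 30, 50, 70 and 90 vials. These match the column heads of the power table in Section 10, which begin "Cohort 1 (30 total vials".

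**Step 2: split at the third dose.** Share outside the window = vials at 24 h / total vials.

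| Cohort | 0 / 8 / 24 h | Total | Before the 24 h dose | At 24 h | Share at 24 h |
|---|---|---|---|---|---|
| 1 | 10 / 10 / 10 | 30 | 20 | 10 | 33.3% |
| 2 | 10 / 10 / 30 | 50 | 20 | 30 | 60.0% |
| 3 | 10 / 30 / 30 | 70 | 40 | 30 | 42.9% |
| 4 | 30 / 30 / 30 | 90 | 60 | 30 | 33.3% |
| All, 3 patients each | | 3 × 240 = 720 | 3 × 140 = 420 | 3 × 100 = 300 | 300/720 = 41.7% |

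Inside the window cohorts 1 and 2 both receive 10 + 10 vials. The only planned difference between them is the dose at 24 hours.

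**Step 3: can part of the third dose fall inside?** Minimum nebulisation time = vials × 2.2 / 0.3. For 10 vials this is 73 minutes and for 30 vials 220 minutes. A dose started at 24 hours runs wholly past the window.

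**Step 4: does the undefined clock start matter?** Consent, randomisation, study initiation and first dose all fall at or before time 0 of the dosing schedule. A 24-hour window from any of them ends at or before the scheduled third dose.

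**Step 5: sensitivity to reduced doses.** Section 8.7 allows 30-vial doses to drop to 20 or 10. If all of them did, the shares would be (10 + 20 + 20 + 20) / (30 + 40 + 50 + 60) = 70/180 = 38.9%, or 40/120 = 33.3%.

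**Step 6: after the change.** A window that runs past the third dose covers 720 of 720 planned vials, and exposure inside it becomes 30, 50, 70 and 90 vials.

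**The case against.** The strongest reply is that nothing is lost. The same sentence summarises these events over the whole study, and AEs are recorded until 28 days after treatment ends (Section 9.2). The relationship-to-treatment summary has no time limit, and the causality categories in Section 9.3.2 rest on timing relative to administration. This stands, and it confines the point to one descriptive window.

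A reader might infer that the trial cannot judge whether the step from cohort 1 to cohort 2 was tolerated. The documents do not support that. Section 4 bases progression on 48-hour outcomes and reported adverse events, with DSMB review before the TSC decides. Section 8.7 adds daily review of AE and SAE data and a pause if three or more patients develop the same SAE. The table is also by randomisation group, which most naturally means treatment against control, since patients are randomised 3:2 and cohorts are filled in sequence. Even a by-cohort table would say little with three treated patients each: 0/3 events has an exact 95% upper limit of 1 − 0.025^(1/3) = 71%, and 3/3 against 0/3 gives a two-sided Fisher p of 2/20 = 0.10.

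Two further replies carry less weight. The 48-hour rule in Section 9.2 covers a specific list of deteriorations and not all SAEs, so it does not oblige Section 10 to use the same window; it does show what horizon the protocol treats as acute. An SAP could add another window, but the protocol itself fixes this one. Section 10 (Efficacy) does use 24 hours as shorthand for 24 hours after the last dose. If that was meant here, the safety wording still needs correcting.

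**Conclusion.** The point holds in a limited form. The one early summary of SAEs and Grade 3/4 AEs closes at or before the scheduled third dose. It therefore excludes the acute period after 41.7% of planned vials, or between 33.3% and 38.9% if every 30-vial dose is reduced as Section 8.7 allows. The cohort 1 to cohort 2 step adds no exposure to the window. The 41.7% assumes the full planned escalation with three treated patients per cohort, and the window's end assumes a clock that starts no later than the first dose.

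It would go too far to say that third-dose safety goes unreported, that escalation decisions are blind to it, or that the third dose is generally the largest. It is strictly the largest only in cohort 2 and equals the largest earlier dose in the other three. No hypothesis test or escalation rule rests on this table. The correction is worth making because the stated window does not fit the dosing schedule.

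**What to change.** In Section 10 (Safety), define the clock start as study initiation and say which event that is, with an equivalent time zero for controls. Replace the 24-hour window with *the first 48 hours after study initiation*, applied identically in both arms. If study initiation coincides with the first dose, this gives 24 hours of cover after an on-schedule third dose and agrees with the 48-hour recording in Section 9.2 and the DSMB timing in Section 8.7.

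Section 8.7 lets a missed dose be given later, and a fixed 48-hour window would then give less than 24 hours of cover. For treated patients whose third dose is delayed, also report events to 24 hours after the last dose actually given. If a 24-hour summary is kept, label it as covering the first two doses only.

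The cost is a wording change and one extra tabulation. The events are already recorded, and dosing and conduct are unaffected.
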